## Abstract

**Background:**

Non-alcoholic fatty liver disease (NAFLD) is an emerging epidemic that affects approximately half of all people with type 2 diabetes. Those with type 2 diabetes are a high-risk NAFLD subgroup because of their increased risk of clinically significant liver-related outcomes from NAFLD which include hepatocellular carcinoma, cirrhosis-related complications and liver disease mortality. They may benefit from early detection of disease as this would allow at risk patients to access hepatocellular carcinoma surveillance, emerging drug trials for NAFLD and specialist hepatology care prior to emergence of liver-related complications.

**Methods:**

This is a prospective cohort study aimed at incorporating and assessing a community care pathway for liver fibrosis screening into routine care for type 2 diabetes. Patients undergo a point of care assessment of hepatic steatosis and stiffness using FibroScan at the time of the routine diabetes appointment or when attending the clinic for blood tests in preparation for this appointment.

**Discussion:**

We propose that implementation of a community-based NAFLD diagnosis, risk-stratification, and referral pathway for people with type 2 diabetes is feasible, will provide earlier, targeted detection of advanced fibrosis, and reduce unnecessary referrals to hepatology outpatients for fibrosis risk assessment. Our study will provide important information about the feasibility of establishing a NAFLD pathway for people with type 2 diabetes in primary care. Ultimately, our findings will help direct spending and resource allocation for NAFLD in a high-risk population. Regular evaluation by stakeholders during implementation will help to create a reliable and sustainable community care pathway and establish a perpetual cycle of learning in primary care.

**Trial registration:**

ANZCTR, ACTRN12621000330842. Registered 23 March 2021.

**Supplementary Information:**

The online version contains supplementary material available at 10.1186/s12913-022-07808-7.

## Novelty statement

There is an inconsistent approach to testing for and evaluating NAFLD in the community, which raises concerns that high-risk subgroups, including people with type 2 diabetes, are under-investigated and managed for advanced hepatic fibrosis.This study describes a method for implementing and evaluating a “real-world” referral pathway for the emerging epidemic of NAFLD.We have designed this community care pathway to be regularly evaluated by stakeholders during its implementation and through this review process to create a perpetual cycle of learning in primary care.

## Background

Non-alcoholic fatty liver disease (NAFLD), the liver component of a group of conditions associated with metabolic dysfunction, is present in 47–64% of people with type 2 diabetes (T2D) [1]. NAFLD is a heterogeneous disorder with variable rates of liver disease progression and clinical outcomes [2–4]. Although the leading causes of death are cardiovascular disease and extrahepatic malignancy, 5–10% of people with NAFLD develop complications of advanced liver disease over 10 to 20 years [5, 6]. Among people with T2D, up to one third (15–30%) are at risk of clinically significant fibrosis [7–9] and there is a more than 2-fold increased risk of cirrhosis-related complications and liver disease mortality [10]. As a result, there is increasing recognition that an assessment of NAFLD and the severity of liver disease needs to be incorporated into the routine care of patients with T2D [7, 9, 11].

Several peak bodies recommend identifying people with T2D or metabolic syndrome at risk of advanced chronic liver disease (CLD) [12–14]. In the absence of a structured approach to screening and risk stratification, the diagnosis of NAFLD in these high-risk people is inconsistent and often occurs incidentally, during investigation of other clinical concerns [15, 16]. These patients are more likely to have severe liver disease and hepatocellular carcinoma (HCC) at the time of diagnosis [17], which greatly limits available therapeutic options. In contrast, the majority of patients currently referred to hepatology clinics for evaluation of NAFLD do not have advanced fibrosis and could be appropriately managed in primary care with attention to cardiometabolic risk factors. At present there is limited data regarding how best to support the targeted detection of patients at highest risk of CLD among the immense number of people with T2D.

The most important prognostic marker for adverse liver outcomes and overall mortality is the presence of advanced fibrosis [5, 6, 18, 19], which can be assessed using combinations of non-invasive tests [19, 20]. Clinical judgement and liver enzymes are poor discriminators of NAFLD severity. In people with T2D, transient elastography can identify the subgroup of individuals with a high risk of advanced fibrosis. Screening studies in community [21] or hospital-based T2D clinics [22, 23] have shown that, using a liver stiffness measurement (LSM) threshold of ≥9.6 kPa, advanced fibrosis was confirmed in 40–50% of patients who received a liver biopsy [24, 25]. Using a 8.0 kPa cut-off to exclude advanced CLD has a sensitivity of 93% in NAFLD [26]. Transient elastography can be performed as a rapid point-of-care test and allows estimation of steatosis by controlled attenuation parameter (CAP) at the same time. Although clinical guidelines endorse the use of simple scores (NAFLD Fibrosis Score (NFS) and Fibrosis 4 Index (FIB-4)) for initial assessment of fibrosis, a substantial proportion (36–63%) of patients fall into an “indeterminate risk” category and require second-line assessment with transient elastography [8, 27].

To date, few studies have examined strategies to introduce routine assessment of fibrosis into T2D care pathways. We propose that implementation of a community-based NAFLD diagnosis, risk-stratification, and referral pathway for people with T2D is feasible, will provide earlier, targeted detection of advanced fibrosis, and reduce unnecessary referrals to hepatology outpatients for fibrosis risk assessment.

## Methods/design

### Overview

The non-alcoholic fatty liver disease: implementing the right care in the right place at the right time (NAFLD-RRR) study is a quasi-experimental study with a prospective intervention and historical control group. The intervention aims to incorporate a community care pathway for liver fibrosis screening into routine care for T2D. The study protocol (Version 6, 9th Feb 2022) includes in-depth phenotyping of participants including demographic details, metabolic co-morbidities, anthropometric measurements, alcohol consumption, smoking status, current medications and average daily physical activity. During a single assessment, liver steatosis and stiffness are measured using an EchoSens FibroScan Mini+ 430. The patient record is interrogated for the most recent haematological and biochemical parameters, lipid profile, and abdominal radiology. Patients are also asked for consent to collect health care usage data from a national Government agency, Services Australia. These data will be used to determine longitudinal health outcomes and facilitate an accurate and thorough analysis of health care usage and economic costs.

### Study aims

The primary aims of the study are to determine whether an integrated diagnostic and risk stratification pathway for people with T2D in primary care:

A1: increases the rate of detection of NAFLD and.

A2: increases the number of people identified with advanced fibrosis/cirrhosis.

The secondary aims are to determine whether the pathway:

A3: links people with NAFLD to the “right care” tailored to individual needs (referral of people with increased risk of advanced liver fibrosis to Hepatology clinics) and.

A4: increases the rate of surveillance for HCC among people with a diagnosis of cirrhosis.

We will also evaluate:

A5: the sustainability of the intervention in the current health care system in relation to resource use and costs, and.

A6: the utility of pathway-specific template letters to the General Practitioner (GP) and diabetes specialist that summarise the clinical findings and provide brief recommendations for management and follow-up.

### Hypotheses

Compared with patients receiving usual care, people with T2D using the NAFLD pathway are hypothesized to benefit in the following ways:

H1: increased identification of NAFLD.

H2: increased identification of people at increased risk of advanced fibrosis/cirrhosis.

H3: increased referral of people with ‘high-risk’ NAFLD to Hepatology clinics and reduced referrals of ‘low-risk’ NAFLD to Hepatology clinics.

H4: increased surveillance for HCC among people with a diagnosis of cirrhosis.

H5: resource use and net-costs of the new pathway for NAFLD diagnosis and risk stratification in the community will be sustainable relative to existing usual care.

H6: GP knowledge and confidence in the recognition, diagnosis, risk stratification and management of NAFLD in their practice population will improve.

### Design and setting

This clinical trial examines the implementation of a diagnostic and risk stratification pathway for NAFLD in people with T2D. Sequential participants will be recruited to the NAFLD-RRR pathway and followed for up to 10 years to monitor their health outcomes. The detection of patients with NAFLD ± advanced fibrosis and the surveillance for HCC among “high-risk” patients will be compared to patients receiving “usual care”.

Due to the high prevalence of NAFLD and advanced fibrosis in people with T2D, it is not appropriate to conduct a randomized study of screening and risk stratification versus no intervention. All people attending the community diabetes clinics will be offered participation in the study. Study outcomes will be compared to a cohort who received “usual care” at the community diabetes clinics in the 12-months prior to implementation of the NAFLD-RRR pathway. The medical records of “usual care” patients will be audited to determine the number of people with a recorded diagnosis of NAFLD, whether an assessment of liver disease severity was performed, and the number of people referred to a liver clinic.

The study will be conducted in 3 “Beacon” diabetes clinics in the Metro South hospital and health services district (HHS), where people who are referred by their GP for specialist management of T2D are offered specialised care in a primary care setting. The Beacon model for people with complex T2D is delivered through community-based general practices where GPs with a special interest (GPwSIs) and advanced training in diabetes work alongside an endocrinologist and diabetes nurse educator [28]. The model is an alternative to standard hospital outpatient review and is fully integrated, with primary care providers and specialists co-located to provide effective, cost-efficient and patient-centred care [29]. In this model the GPwSIs take their enhanced skills back to their routine practice, so they become a referral point and source of knowledge for colleagues, potentially reducing referrals to specialist clinics. Prior to developing and implementing the NAFLD-RRR pathway, diabetes clinic/community clinicians (*n* = 24) were invited to participate in focus group discussions to obtain information about preferences and strategies for learning, support and communication [30].

The Metro South HHS covers the south side of Brisbane and has a catchment area of 3860 km^2^. It provides healthcare to more than one million people, which is 23% of the state of Queensland’s population.

### Participants

#### Eligibility criteria

Eligible participants are (1) adults aged ≥18 years; (2) who are referred to a Beacon diabetes clinic in Metro South HHS for management of T2D.

#### Exclusion criteria

Individuals will be excluded if they are (1) unable to provide informed consent; (2) pregnant and/or; (3) have a diagnosis of advanced cardiac disease or another terminal illness, or known chronic liver disease and are undergoing follow-up with a Hepatology clinic.

### Participant recruitment

The diabetes clinic appointment databases will be prescreened for eligible participants who are scheduled for routine review by a diabetes clinician. Persons identified as eligible will be contacted via text message and then telephoned in the 2 weeks preceding their appointment to discuss the study and offer participation.

Scheduled participants will be invited to be screened for NAFLD when they attend a Diabetes clinic appointment or when they have their fasting blood tests performed in preparation for their Diabetes clinic appointment, using FibroScan to assess steatosis (CAP score) and liver fibrosis (liver stiffness measurement, LSM) (Fig. 1).

**Fig. 1 Fig1:**
[figure not shown]
Flow diagram of initial recruitment strategy and patient flow through the NAFLD-RRR pathway. USS Ultrasound Scan; LSM Liver Stiffness Measurement; CAP Controlled Attenuation Parameter; LFTs Liver Function Tests; FIB-4 Fibrosis-4 Score; NFS Non-alcoholic Fatty Liver Disease Score; GP General Practitioner

### Intervention

#### FibroScan

Transient elastography (using FibroScan) has been extensively evaluated; a liver stiffness threshold of 6.5–7.9 kPa has approximately 90% sensitivity in excluding advanced (stage 3–4) fibrosis, whereas LSM > 12–15 kPa is typically present with cirrhosis [31–35]. Transient elastography will be performed by a trained clinician as a point-of-care test, concurrently with the diabetes clinic appointment or when the participant attends for a scheduled blood test, making it easier for participants to have the test performed.

To obtain accurate results from the FibroScan assessment participants will be advised to fast for 3 h before the scheduled time of examination. Clear guidance will be provided to participants regarding fasting and withholding of T2D medications. If the FibroScan appointment is prior to 10 am, participants will be advised to fast overnight and withhold T2D medications until after the examination. If the FibroScan appointment is 10 am or later, participants will be advised to have an early breakfast, and to take their usual T2D medications, and then to fast for 3 h prior to the scan. Participants will be advised to bring a snack and all medications to clinic so that as soon as the FibroScan is completed, they can eat and take their T2D medications as required.

In around 9–15% of examinations, a valid LSM cannot be obtained because a participant’s body habitus or skin to liver capsule depth prevents an accurate assessment [8, 36]. Should this occur, the need for further review of these participants will be determined by the diabetes and study clinicians based on the history, blood tests and imaging available.

#### Other clinical information

At the FibroScan assessment the study clinician will assess girth and document alcohol consumption using the short form AUDIT [37] to quantify alcohol misuse, based on 3 questions posed to patients about their consumption habits. A short medical history form (Table 1) will be completed to obtain information about the following: prior diagnosis, management and follow-up of fatty liver; prior hepatology review; year of diagnosis of T2D; presence of other cardiometabolic risk factors (obesity, hypertension, dyslipidaemia); presence of cardio- cerebro- or peripheral vascular disease, history of cancer; mental health; family history of fatty liver; medications; current employment status (full-time, part-time, unemployed, disability pension); sociodemographic data (e.g. marital status, education level, country of birth, place of residence).

**Table 1 Tab1:** Clinical data collected at NAFLD-RRR appointment

Demographic information	
Age	
Ethnicity	
Language spoken at home	
Country of birth	
Sex	
Menopausal status – pre, peri, post	
Relationship status – single, married or de factor, divorced/separated, widowed	
Level of education – junior, senior high school, TAFE, university	
Employment status – full time, part time, unemployed, disability pension	
Medical history	
Year T2D diagnosed	
Cardiometabolic risk factors – obesity, hypertension, dyslipidaemia,	
Metabolic comorbidities – cardiovascular disease, atrial fibrillation, cerebro- and/or peripheral vascular disease, obstructive sleep apnoea, chronic kidney disease, gout	
History of malignancy – primary cancer type and year diagnosed	
Patient-reported NAFLD	
Previous diagnosis of NAFLD	
Year NAFLD diagnosed	
Investigations for NAFLD diagnosis	
Previous hepatology review	
Current Medications	
Lifestyle	
Smoking status – yes/no/previous and pack-years	
Alcohol consumption	
Physical activity	
Depression Inventory	
Family history of liver disease	
Fatty liver disease	
Liver disease	
Cirrhosis	
Liver cancer	

The patient will be diagnosed with NAFLD on the basis of the FibroScan CAP score (CAP score ≥ 248 dB considered as likely steatosis based on cut-offs determined in a large meta-analysis) [38] and stratified to low or high risk of clinically significant fibrosis on the basis of the FibroScan liver stiffness measurement (LSM).

No NAFLD: Participants with CAP score < 248 dB and LSM < 8 kPa will be classified as “no NAFLD”. A letter will be sent to the patient’s GP and diabetes specialist advising a repeat FibroScan or liver ultrasound in 3–5 years if appropriate, to screen for development of NAFLD. Participants will be informed of their FibroScan result at the NAFLD-RRR appointment and advised to follow up with their GP.

NAFLD with low risk of clinically significant fibrosis: Participants with CAP score ≥ 248 dB and low FibroScan score (LSM < 8.0 kPa) will be classified as ‘Low Risk’. A letter will be sent to the patient’s GP and diabetes specialist advising a repeat FibroScan in 2–3 years if appropriate, to assess for development of clinically significant fibrosis. If liver enzymes are abnormal, the letter to the participant’s GP will include guidance for further evaluation of abnormal liver enzymes.

High risk of clinically significant fibrosis: Participants with LSM ≥8.0 kPa will be classified as ‘High Risk’. The study clinician will advise the patient (and GP and diabetes specialist via letter) that Hepatology referral is recommended. A letter will be sent to the patient’s GP advising them to arrange a Hepatology Clinic referral. To assist GPs with this process, referral guidelines will be included with the patient’s letter and FibroScan result. If advanced fibrosis is confirmed in the secondary care hepatology clinic, the patient may be offered ongoing hepatology follow-up that may involve HCC and variceal surveillance programs.

For all patients with NAFLD, the letter to the GP and diabetes specialist will provide recommendations regarding management of NAFLD with ongoing assessment and management of cardiometabolic risk factors and lifestyle intervention with consideration of referral to a dietician, exercise physiologist and psychologist for assistance with weight management and increased physical activity. Patients diagnosed with NAFLD at the study clinic visit will receive a patient letter at the conclusion of the clinic visit. This letter advises patients to make an appointment to see their GP to further discuss the recommendations advised by the study team. The template letters are provided in Supplementary Figs. 1-4.

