### Participant outcomes

#### Primary outcomes

***Detection and documentation of NAFLD in people with T2D.*** A diagnosis of NAFLD will be made following a participant’s FibroScan with a CAP score ≥ 248 dB, with documentation in a letter to the patient’s GP and Diabetes Specialist.***Detection and documentation of significant liver fibrosis in people with T2D.*** This will be calculated based on the number of participants who receive a diagnosis of significant fibrosis (LSM ≥8.0 kPa), with documentation in a letter to the patient’s GP and Diabetes Specialist.

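### The first primary outcome counts all-cause steatosis (CAP ≥248 dB) as NAFLD in the pathway group, while usual care counts a recorded NAFLD diagnosis, so the two groups do not measure the same thing

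*Protocol article*

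**What the plan says.** **Diagnosis in the pathway group.** Other clinical information gives the rule: "The patient will be diagnosed with NAFLD on the basis of the FibroScan CAP score". It describes the cut-off in these terms: "CAP score ≥ 248 dB considered as likely steatosis based on cut-offs determined in a large meta-analysis". The first primary outcome uses the same rule and adds only that the result is documented in a letter: "A diagnosis of NAFLD will be made following a participant’s FibroScan with a CAP score ≥ 248 dB". The three result categories in the Intervention section (no NAFLD, low risk, high risk) use CAP and liver stiffness (LSM) and nothing else.

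**Who can enter.** Participants are adults "who are referred to a Beacon diabetes clinic in Metro South HHS for management of T2D". There is no alcohol criterion. The liver-disease exclusion covers people with "known chronic liver disease and are undergoing follow-up with a Hepatology clinic".

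**Alcohol data.** At the scan visit the study clinician will "document alcohol consumption using the short form AUDIT [37] to quantify alcohol misuse". No threshold is given, and no category or outcome refers to the score.

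**Usual care.** Under Design and setting, the records of the historical cohort are "audited to determine the number of people with a recorded diagnosis of NAFLD". Under Secondary outcomes, controls have the same eligibility and exclusion criteria apart from consent. For alcohol, the audit notes only whether consumption is recorded at all.

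**The concern.** The outcome is named for a disease defined partly by what does not cause it, but it is measured by a test that is blind to cause. A participant whose AUDIT answers show alcohol misuse, or who has another known liver disease outside Hepatology follow-up, is eligible. If CAP is 248 dB or more, the rule leaves no choice but to count that person as NAFLD.

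The two groups are also measured differently. In the pathway group every scan at or above the cut-off counts. In the usual-care group a case counts only if a clinician wrote down NAFLD, and a clinician who knew that the patient drank heavily could have recorded the fatty liver under another name. Both groups are drawn from the same kind of patient, so this difference in definition feeds directly into the comparison for Aim A1 and hypothesis H1.

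The label also carries into the referral outcomes under Secondary outcomes, which speak of high-risk and low-risk NAFLD. The high-risk category rests on LSM ≥8.0 kPa alone and the low-risk category on CAP plus LSM, so neither considers cause. The economic outcome, cost per appropriate referral, builds on these referrals.

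**Working it through.** **1. The plan's own figures** (Sample size and statistical power)

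- Expected CAP-positive participants: 400 × 0.60 = 240.
- Expected with advanced fibrosis: 240 × 0.20 = 48.
- Wilson 95% interval for 48/240, with z = 1.96: (p + z²/2n ± z√[p(1−p)/n + z²/4n²]) / (1 + z²/n).
- Centre: (0.2 + 0.0080) / 1.0160 = 0.2047. Half-width: 1.96 × √(0.000667 + 0.0000167) / 1.0160 = 0.0504.
- Result: 15.4 to 25.5%, as the protocol states. There is no arithmetic error. The point concerns what is being counted.

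**2. Can another cause of steatosis be filtered out at any step?**

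| Step | Condition stated | Removes other causes? |
|---|---|---|
| Eligibility | Adult, referred for T2D | No |
| Exclusion | Known liver disease and under Hepatology follow-up | Only that subset |
| Diagnosis | CAP ≥248 dB | No |
| Result category | CAP and LSM | No |
| Letter to GP, low-risk group | Guidance if liver enzymes are abnormal | Does not revise the count |
| Primary outcome 1 | CAP ≥248 dB and a letter | No |

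If the exclusion were read more widely, as covering all known chronic liver disease, alcohol misuse and unrecognised disease would still pass through.

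**3. Which outcomes are exposed?**

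- Primary outcome 1 (NAFLD): exposed.
- Primary outcome 2: defined as significant fibrosis in people with T2D, LSM ≥8.0 kPa, with no NAFLD condition. Not exposed.
- Referral of high-risk and low-risk NAFLD: the label is exposed.

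**4. Illustration of size.** Let s be the share of CAP-positive participants with alcohol misuse or another known liver disease. The protocol gives no value, so s is an assumption. Affected = 240s. Rate without them = 240(1 − s)/400. Intervals are Wilson 95%.

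| s (assumed) | Affected | Remaining | Rate without them | 95% interval |
|---|---|---|---|---|
| 0 | 0 | 240 | 60% | 55.1 to 64.7% |
| 5% | 12 | 228 | 57% | 52.1 to 61.8% |
| 10% | 24 | 216 | 54% | 49.1 to 58.8% |
| 15% | 36 | 204 | 51% | 46.1 to 55.9% |

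Each further 1% of s affects 2.4 people (240 × 0.01) and lowers the rate by 0.6 percentage points (2.4/400). At s = 30% the figures would be 72 people and 42%.

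**5. Precision of the fibrosis estimate.** With 204 rather than 240 in the denominator, a 20% fibrosis rate (41/204) has a Wilson interval of 15.2 to 26.1%, against 15.4 to 25.5%. Precision hardly changes.

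**The case against.** The best case for the plan has four parts.

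*The error may also occur in usual care.* Nothing says that usual-care clinicians ruled out alcohol before recording NAFLD, so recorded diagnoses may contain the same error. This stands. A reader might infer that the overstatement arises in the pathway group only, but the documents do not show that. Inflation of the difference is probable, because scanning everyone finds more steatosis of every cause. Its net size is unknown.

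*Drinkers with T2D may still have metabolic steatosis.* The Background describes NAFLD as the liver component of conditions linked to metabolic dysfunction, and every participant has T2D. Alcohol misuse does not show that metabolic steatosis is absent. This stands too, so 51–57% must not be read as the true NAFLD rate. The documents also do not show that heavy drinkers will be recruited, only that they are not excluded.

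*The conclusion on H1 would probably survive.* This is likely. The only historical figure, below 5%, is attached to the advanced-fibrosis rate, so it is not a firm benchmark for NAFLD detection. If it were used as one, 51% would still be far above it. The harm is to the meaning and size of the estimate.

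*A fuller document may contain a rule.* Figure 1, the template letters and the full protocol are not shown. However, the article states the outcome definition outright in two places. That definition has been fixed, and is not a detail left for elsewhere.

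**Conclusion.** The point holds as one of outcome definition and comparability. As written, the first primary outcome is all-cause steatosis under the name NAFLD, set against a clinician-recorded diagnosis in usual care. This probably inflates the H1 difference and mislabels some referrals in the two NAFLD referral outcomes.

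The size cannot be derived from the protocol. On an assumed share of 5–15%, it is 3 to 9 percentage points of the expected 60% (12–36 of 240 people). This is an upper reading for those shares, because it removes everyone with alcohol misuse or another known liver disease, including any who also have metabolic steatosis.

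A reader might go on to infer that the fibrosis outcome is miscounted in the same way. It is not. That outcome, Aim A2 and H2 refer to fibrosis or cirrhosis without requiring NAFLD, so a participant with LSM ≥8.0 kPa is correctly counted whatever the cause.

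**What to change.** **Main change.** In Primary outcomes, name the CAP ≥248 dB outcome *hepatic steatosis*, and word A1 and H1 to match. In the usual-care audit, count any recorded fatty liver, not only entries that say NAFLD. The audit already covers radiological investigations. Both groups then count the same condition, and the remaining difference is how it was found, which is what the intervention changes.

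**Supporting analysis, stated in advance.** In the pathway group, report NAFLD as CAP ≥248 dB with a short AUDIT score below a cut-off that the sponsor fixes beforehand and no other known chronic liver disease. Show the remaining CAP-positive participants in a separate row. Apply the same split to controls only where alcohol is recorded, and state that limit.

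The split should not be the primary comparison. It would remove drinkers from the pathway count wherever AUDIT was completed, but from controls only where the record allows, and so could create an imbalance against the pathway.

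**Cost.** Outcome wording, one derived variable, a slightly wider audit item, and a slightly lower rate under the NAFLD label. AUDIT is already collected. Table 1 has no item for a personal history of other liver disease, but applying the exclusion criterion already requires that check, so its result needs to be kept. Eligibility, visits and clinical care do not change.
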